### Blinding

Before surgery, the surgeon will be blinded to group allocation and will generate radiographic measurements and surgical planning for both uncemented and hybrid surgeries for each patient. All participants will be blinded to the technique utilized. However, a record for medical use will be available, upon request, in the hospital medical file. The surgeon cannot be blinded during the surgical procedure because this is a clinical trial of surgical treatment techniques. To minimize observer bias, all postoperative clinical and functional evaluations will be performed by independent researchers blinded to participant group allocation and postoperative radiographs. Postoperative radiographs will be analyzed by a separate researcher with experience in hip surgery, who will be blinded to preoperative measurements, surgical planning, and postoperative clinical and functional evaluations.

Therefore, blinding was applied in all 3 stages and across all 3 levels, which is known as triple-blinding. The surgeon is blinded to the preoperative evaluation and performs surgical planning without knowledge of which implant will be used. Blinding is broken at the time of surgery. Participants remain blinded throughout the study. Two types of evaluators are involved: an imaging evaluator and a clinical evaluator. The postoperative evaluator, using the X-ray, is blinded to the preoperative evaluators and the postoperative clinical evaluation. The postoperative clinical evaluator is blinded to both group evaluation and radiographic examination. A description of each researcher involved in the study is provided below in Table 1.

**Table 1. T1:** Description of each role in the study.

Research role	Action	How was blinding implemented	Breach of blinding
Surgeon	Independent surgical planning for every patient, generating two archives: hybrid construct and uncemented construct	The surgeon received the digital radiograph of each patient and was unaware of the allocation group	Blinding was relieved only at the time of surgery, when the surgeon received only the applicable copy of the digital plan previously generated, according to the random allocation
Patient	Remained blinded to the allocation group throughout the study	The patient received no information regarding group allocation. The discharge summary from the hospital contained only a reference that he was participating in the THA^a^ study and that details about the implant were available on file upon request	No cases of unblinding were observed
Evaluators			
Clinical evaluators	Applied questionnaires and physical exam, blinded to the allocation group and postoperative radiographs	This group of doctors was called in exclusively for this task during the study	No cases of unblinding were observed
Radiographic evaluators	An orthopedic surgeon analyzed exclusively postoperative radiographs using a custom extraction questionnaire	This evaluator had no access to preoperative radiographs, surgical planning, allocation group, clinical evaluations, or the patient themselves	No cases of unblinding were observed

a THA: total hip arthroplasty.

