## Methods

### Study Design and Setting

This study was written according to the Standard Protocol Items: Recommendations for Interventional Trials (SPIRIT) guidelines (Checklist 1) for protocols of randomized clinical trials. The proposal is a single-center, single-surgeon, single-approach, pragmatic, double-blinded, prospective randomized trial to analyze the differences between uncemented hip replacement and the hybrid (femoral cemented) hip replacement.

Two different types of hip implants will be used for comparison: the Maxima Cemented Vincula Stem (Víncula, Rio Claro, SP, Brazil) and the Taper Uncemented Primary Stem (Víncula, Rio Claro, SP, Brazil). Patients and evaluators will be blinded to group allocation: the hybrid group (HG) and the uncemented group (UG). A total of 120 patients will be enrolled in this study and randomly allocated to each group in a 1:1 ratio.

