#### Femoral Procedure in the HG

Patients allocated for hybrid arthroplasty will undergo a surgical procedure consisting of positioning the femur by internal rotation of 90° and flexion of the hip. The Schumacher-type retractors will be positioned under the anterior surface of the femoral neck, and the remaining capsule and tendons of the piriform fossa will be resected. Following this, the metaphyseal bone with a box-type chisel will be removed, and a cylindrical femoral starting broach will be used to enlarge the canal. According to the surgical plan, the femoral canal will be prepared with successive femoral rasps until adequate stability and restoration of the anatomical parameters of offset and length are achieved.

Following the surgical plan, a femoral neck and head test will be done. Hip reduction, stability test at the extremes of the range of motion (ROM), assessment of limb length, soft tissue tension, and dislocation of the test prosthesis will be done, and the hip reduced to assess stability, limb length restoration, and soft tissue tension. After ensuring adequate size, the surgeon will dislocate the hip joint again and mark it with electrocautery for guidance during definitive implant positioning. Further removal of bone at the Gruen zone I will be undertaken with a curette for adequate cement penetration. A cement restrictor will then be placed, obliterating the femoral canal 2 cm distal to the tip of the femoral stem. Copious irrigation of the canal and thorough cleansing and drying will be performed to remove all blood and medullary content. Cementation of the femoral canal using a retrograde technique with a cement pistol and two cements will be done under pressure. The polished double wedge cemented stem (Máxima, Vincula, Rio Claro, Brazil) will be introduced at a constant speed with a distal centralizer to the planned position. The target anteversion will be 15° with central alignment to the femoral axis.

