#### Femoral Procedure in the UG

Patients allocated to uncemented arthroplasty will undergo a surgical procedure consisting of positioning the femur in 90° of internal rotation with hip flexion. Schumacher-type retractors will be placed beneath the anterior surface of the femoral neck, and the remaining capsule and tendons of the piriform fossa will be resected. Subsequently, the metaphyseal bone will be removed using a box-type chisel, and a cylindrical femoral starting broach will be used to enlarge the canal. The femoral canal will be reamed with successive femoral rasps, according to the plan, until adequate stability and restoration of the anatomical parameters of offset and length.

A testing femoral head will be assembled, and the hip will be reduced. Hip stability, limb length restoration, and soft tissue tension will be assessed. After ensuring adequate size, the surgeon will dislocate the hip joint again and mark it with electrocautery for guidance during definitive implant positioning. The uncemented titanium triple wedge plasma-sprayed femoral stem (Taper, Vincula, Rio Claro, Brazil) will be introduced by hammering with a press-fit technique down to the planned position. The target anteversion will be 15° with central alignment to the femoral axis.

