### Secondary Outcomes

Secondary outcomes will include comparisons of QoL, joint mobility, function, satisfaction, and pain before and after the surgery, as well as radiographic parameters extracted from the immediate postoperative radiograph. The annual frequency of revision surgeries will be recorded.

QoL will be evaluated using 12-Item Short Form Health Survey version 2 questionnaire [21]. QoL is defined as an individual’s perception of their position in life in the context of the culture and value systems in which they live and about their goals, expectations, standards, and concerns [21]. The 12-Item Short Form Health Survey is an instrument for measuring QoL composed of 12 items that assess eight different dimensions of influence on QoL, considering the individual’s perception of aspects of their health in the last 4 weeks [21]. Each dimension’s score is summed up, and the final score can be between 0 and 100; the higher the score, the better the QoL [22].

Participant satisfaction assessment will be measured using a 10-point numerical rating scale ranging from 1 (very dissatisfied) to 10 (completely satisfied) [23].

Other aspects of health, such as pain, will be evaluated through the Visual Analog Scale. The Visual Analog Scale provides a simple and efficient measure of pain intensity and is used when a fast pain index that can be assigned to a numerical value is needed [24].

Radiographic parameters will include the ability to restore anatomical normality parameters on postoperative radiographs according to the surgical plan (namely the limb length discrepancy, the horizontal off-set of the hip, difference between the back of the prosthesis and the tip of the trochanter, inclination of the acetabular component, and the difference between offset obtained to the normal side) all of this using the Peekmed surgical planning software.

The annual frequency of revision surgery will be observed starting from 1 year after surgery and annually until 5 years, and up to 10 years.

All questionnaires will be administered by examiners blinded to the surgical procedure. Questionnaires will be completed using digital devices (computer or tablet).

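### The radiographic reader cannot be blinded to allocation as claimed, because the films show the stem; separately, one offset parameter has no stated reference hip in bilateral patients

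*Protocol article*

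**What the plan says.** The article describes the radiographic reader's blinding in three places, and they do not agree.

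- **Study Design and Setting** covers all evaluators: "Patients and evaluators will be blinded to group allocation: the hybrid group (HG) and the uncemented group (UG").
- **Table 1** says of the radiographic evaluator: "This evaluator had no access to preoperative radiographs, surgical planning, allocation group, clinical evaluations, or the patient themselves". The entry for breach of blinding in the same row is "No cases of unblinding were observed".
- **The Blinding text** describes this reader as a separate researcher experienced in hip surgery, "who will be blinded to preoperative measurements, surgical planning, and postoperative clinical and functional evaluations". Allocation is not in that list. A second description later in the section also omits it, while the clinical evaluator is expressly called blind to group. The section nevertheless concludes: "Therefore, blinding was applied in all 3 stages and across all 3 levels, which is known as triple-blinding".

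The two femoral procedures are described separately. In the hybrid group: "Cementation of the femoral canal using a retrograde technique with a cement pistol and two cements will be done under pressure", with a restrictor below the stem tip and a distal centralizer. In the other group, the implant is "The uncemented titanium triple wedge plasma-sprayed femoral stem", driven in by press-fit.

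On the second point, Textbox 1 admits both unilateral and bilateral arthritis. Secondary Outcomes lists five radiographic parameters, the last being "the difference between offset obtained to the normal side", with no qualification for bilateral disease.

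**The concern.** Keeping the allocation list from a reader blinds that reader only if the material being read does not itself reveal the arm. Here the arms differ in the femoral stem and its fixation, and the reader's task is to examine films of that stem.

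What is at stake is how the radiographic results are presented. According to the Results section, a first analysis covering radiographic and intraoperative findings was done in November 2025, with publication expected in the first half of 2026. Radiographic comparisons are therefore among the first results to appear, and they would carry an assessor-blinding label they cannot support. The Discussion also cites blinding of the evaluators as a safeguard when it addresses the manufacturer's discount and equipment, so an overstatement weakens that argument too.

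The offset point is separate. A parameter defined against a normal hip has no evident reference when the other hip is also arthritic.

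**Working it through.** **Blinding.** This is a comparison of statements; no arithmetic decides it.

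1. *Who reads?* An orthopedic surgeon (Table 1) with experience in hip surgery (Blinding).
2. *What is read?* Postoperative radiographs only (Table 1). No masking or cropping is described.
3. *What differs on the films?* In one arm, a cemented stem with cement in the canal, a restrictor and a centralizer. In the other, an uncemented titanium stem of a different shape. The acetabular component is common to both arms.
4. *Does that difference reveal the arm?* Yes. The groups are defined by the femoral construct, so recognising it is knowing the allocation.
5. *Do the descriptions agree?* Study Design and Setting and Table 1 include allocation among the things concealed from this reader. Both descriptions in the Blinding text leave it out.
6. *Is the rest of the reader's blinding disproved?* No. Nothing contradicts blinding to preoperative films, planning and clinical findings.

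**Scope.** All 120 patients receive one of the two stems, so in principle the issue applies to 120 of 120 sets of films. It does not reach the sample size, which rests on the Harris Hip Score. That calculation reproduces:

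n per arm = 2 × (1.960 + 0.842)² × (10.5 / 5.39)² = 2 × 7.85 × 3.795 ≈ 59.6, rounded up to 60, or 120 in total, with power 0.803 by the normal approximation.

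**Normal-side offset.** The documents do not give the share of bilateral patients, so the shares below are assumptions. If bilateral patients leave this one comparison, evenly across arms, the evaluable number is 120 × (1 − share). The standardized difference detectable with 80% power at two-sided 0.05 is d = (1.960 + 0.842) × √(2/m), with m per arm.

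| Assumed bilateral share | Without a normal side | Evaluable | m per arm | Detectable d |
|---|---|---|---|---|
| 0% | 0 | 120 | 60 | 0.51 |
| 10% | 12 | 108 | 54 | 0.54 |
| 20% | 24 | 96 | 48 | 0.57 |
| 30% | 36 | 84 | 42 | 0.61 |
| 40% | 48 | 72 | 36 | 0.66 |

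The loss of sensitivity is modest over this range and affects one of the five listed parameters.

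**The case against.** The strongest defence is that Table 1 may mean only that the reader was not given the allocation list. The Blinding text, read alone, never says that this reader is blind to group. That is fair to the Blinding text. It does not rescue the general statement about evaluators in Study Design and Setting or the no-unblinding entry in Table 1, and it confirms that the sections disagree.

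Several limits on the concern stand:

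- **The double-blind label.** A reader might infer that it is wrong too. The documents do not support that: participants and clinical evaluators are blinded, and the Blinding section openly says that the surgeon is not blinded during surgery.
- **Wholly open assessment.** A reader might infer that radiographic assessment has no blinding at all, or that its results are biased. Neither follows. The reader is still kept from the plan, the preoperative films, the clinical findings and the patient. The outcomes are geometric measurements made in planning software, and no direction or size of bias is shown.
- **A concession by the authors.** Keeping postoperative films from the clinical evaluators suggests that the films reveal the arm, but the stated reason is only to limit observer bias. It is supporting inference, not an admission.
- **Undefined radiographic outcomes.** A reader might extend the bilateral point to all five parameters. Only the normal-side offset difference clearly lacks a reference; cup inclination does not use the other hip.
- **Bilateral cases.** A rule for the reference hip may exist in the full protocol or the extraction forms, which are not shown. An arthritic hip can still have a measurable offset, and randomization should balance bilateral cases on average, so the likely harm is noise. What remains is that the article pairs bilateral eligibility with a normal-side outcome without qualification.

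**Conclusion.** The concern holds as a correction to a stated design property. The article claims allocation blinding for the radiographic reader, reports that it was never breached, and builds a triple-blinding claim on it. The reader's own material shows the stem, and the Blinding text's lists do not support the claim. In principle this covers every postoperative film, but only for secondary outcomes.

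The conclusion rests on two assumptions: that a hip-experienced surgeon can tell the two described constructs apart on a radiograph, and that no masking is applied beyond what the article describes. The first is inferred from the surgical descriptions, but is hard to dispute.

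The normal-side point also holds, at a smaller size: one parameter, an unknown number of patients (12 to 36 of 120 at an assumed 10% to 30%), and probable noise rather than demonstrated bias. Primary outcomes, sample size and clinical-evaluator blinding are untouched by either point.

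**What to change.** **Blinding.**

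- In Study Design and Setting, the Blinding text and Table 1, say that the radiographic reader is blinded to preoperative films, surgical planning and clinical data, but not to stem type.
- Remove the no-unblinding entry for that role.
- Qualify the triple-blinding claim, and the Discussion's use of evaluator blinding as a safeguard, in the same terms.
- Report the radiographic secondary outcomes as not blinded to implant.

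The double-blind label can stay.

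**Normal-side offset.** Limit this single parameter to patients with an unaffected opposite hip, and report how many that is in each arm. For all patients, rely on the comparison with the surgical plan, which Secondary Outcomes already includes. Someone other than the reader, such as the data curator, can compute it so that the reader stays blind to the plan.

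**Cost.** Wording changes and one analysis-set definition. No new films, readers, visits or patients are needed. The price is a less favourable blinding claim and fewer patients in one secondary comparison.

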### Interventions

#### Initial Common Procedure for Both Groups

Patients will be admitted on the day before surgery and will undergo 8 hours of fasting before surgery. Antibiotic prophylaxis (cefazolin 2 g) will be administered 1 hour before anesthetic incision (clindamycin 600 mg will be used as an alternative in cases of allergy). Patients will receive 1 g of tranexamic acid administered intravenously.

Surgery will be performed under neuraxial block (spinal anesthesia) with sedation. Clinical measurement of limb length discrepancy will be estimated by the surgeon with the patient in a supine position and recorded, along with all surgical details, in a specific digital form (Multimedia Appendix 4).

On a regular surgical table, the patient will be positioned in the lateral decubitus, with a hip-positioning device supporting the sacrum and both anterior superior iliac spines. Limb length will be reassessed at this position.

Routine aseptic cleansing and preparation will be performed, and sterile surgical fields will be positioned. The limb to be operated on will be degermed with polyvinylpyrrolidone iodine solution (chlorhexidine will be used instead for patients with allergy), and excess solution will be removed with alcohol. Antisepsis with alcoholic polyvinylpyrrolidone iodine solution will be performed by the surgeon, and sterile drapes will be positioned.

The same surgeon will conduct the surgery on every patient using a standard posterolateral approach. The piriformis tendon, along with other external rotators, will be divided from the femur and tagged with an Ethibond® 5 sutures for later transosseous reinsertion. The capsule will be opened with an L-shaped incision and tagged with an Ethibond® 5 running suture for later reinsertion. Posterior hip dislocation and femoral neck osteotomy, according to the surgical plan, will then be executed with a power saw.

Preparation of the acetabulum will begin with full exposure using a long Homann retractor placed anteriorly and inferiorly. A 4.0 Steinman pin will be placed superiorly for soft tissue retraction. Another 3.5 Steinman pin will be placed between the hip capsule and the posteroinferior labrum in the ischium to complete exposure.

The acetabular labrum, periacetabular osteophytes, round ligament and pulvinar tissue, and curtain osteophytes exposing the fovea will be removed. A successive reaming of the acetabulum will be done with a high-torque drill to the planned diameter and adequate bone contact. The prosthesis will be tested to verify positioning and adequate press fit (with a target inclination of 45° and anteversion of 20°). Subsequently, an uncemented acetabular component (Phenon poly II, Vincula, Rio Claro, Brazil) will be inserted through impaction using the press-fit technique. Additional fixation with 2 to 3 acetabular screws will be used as needed by the surgeon, depending on the perception of the press-fit and bone quality. Insertion of a highly cross-linked polyethylene liner will be performed through impaction, followed by confirmation of system stability.

After performing the procedure on the acetabulum, patients will undergo the femoral procedure according to the group to which they were allocated.

#### Femoral Procedure in the HG

Patients allocated for hybrid arthroplasty will undergo a surgical procedure consisting of positioning the femur by internal rotation of 90° and flexion of the hip. The Schumacher-type retractors will be positioned under the anterior surface of the femoral neck, and the remaining capsule and tendons of the piriform fossa will be resected. Following this, the metaphyseal bone with a box-type chisel will be removed, and a cylindrical femoral starting broach will be used to enlarge the canal. According to the surgical plan, the femoral canal will be prepared with successive femoral rasps until adequate stability and restoration of the anatomical parameters of offset and length are achieved.

Following the surgical plan, a femoral neck and head test will be done. Hip reduction, stability test at the extremes of the range of motion (ROM), assessment of limb length, soft tissue tension, and dislocation of the test prosthesis will be done, and the hip reduced to assess stability, limb length restoration, and soft tissue tension. After ensuring adequate size, the surgeon will dislocate the hip joint again and mark it with electrocautery for guidance during definitive implant positioning. Further removal of bone at the Gruen zone I will be undertaken with a curette for adequate cement penetration. A cement restrictor will then be placed, obliterating the femoral canal 2 cm distal to the tip of the femoral stem. Copious irrigation of the canal and thorough cleansing and drying will be performed to remove all blood and medullary content. Cementation of the femoral canal using a retrograde technique with a cement pistol and two cements will be done under pressure. The polished double wedge cemented stem (Máxima, Vincula, Rio Claro, Brazil) will be introduced at a constant speed with a distal centralizer to the planned position. The target anteversion will be 15° with central alignment to the femoral axis.

#### Femoral Procedure in the UG

Patients allocated to uncemented arthroplasty will undergo a surgical procedure consisting of positioning the femur in 90° of internal rotation with hip flexion. Schumacher-type retractors will be placed beneath the anterior surface of the femoral neck, and the remaining capsule and tendons of the piriform fossa will be resected. Subsequently, the metaphyseal bone will be removed using a box-type chisel, and a cylindrical femoral starting broach will be used to enlarge the canal. The femoral canal will be reamed with successive femoral rasps, according to the plan, until adequate stability and restoration of the anatomical parameters of offset and length.

A testing femoral head will be assembled, and the hip will be reduced. Hip stability, limb length restoration, and soft tissue tension will be assessed. After ensuring adequate size, the surgeon will dislocate the hip joint again and mark it with electrocautery for guidance during definitive implant positioning. The uncemented titanium triple wedge plasma-sprayed femoral stem (Taper, Vincula, Rio Claro, Brazil) will be introduced by hammering with a press-fit technique down to the planned position. The target anteversion will be 15° with central alignment to the femoral axis.

